**2.2.2. Group tutoring program:**

The theatre workshops will be compared with a program in the context of a self-contained classroom.

Students with emotional and behavioural difficulties (EBD) have been found to have comorbid academic and behavioural challenges (93, 94). Irrespective of the classroom placement (special or general education classes), the interventions for students with EBD almost exclusively focus on

behavioural management with academic learning being addressed secondarily, if at all (95). These students are often achieving significantly below level as compared to students without disabilities and exhibit underachievement in all academic areas (96). Research also consistently indicates that they do not improve over time and that in some areas (e.g., math) their difficulties increase (see review, (97)). Some subtypes such as externalizing behaviour and attention were more closely associated with academic underachievement. In addition, high school students with EBD in a self-contained setting indicated that overall school adjustment was predictive of academic performance (e.g., (98)). These interventions focused on targeting in-class academic skills associated with attention to the assigned task, good working habits, developing listening skills and academic reading in the classroom setting (93, 98-

100). Therefore, the comparison intervention of the proposed study is an academic in-class intervention that focuses on differentiated academic instruction and improved overall academic adjustment. Each self-contained class will include a core teacher who teaches curricula based on the Quebec Education Program with age appropriate competencies in reading, math, social studies and science content areas. In each classroom assigned to the tutorship intervention, two academic resource assistants will provide weekly in-class support to students for the same length of time than the drama workshop. Individualized student objectives on reading fluency and math will be implemented (one in math and one in reading per student), as it is believed that improvements in these areas will contribute to increased overall achievement, decreased absenteeism, and reduction in emotional and behavioural difficulties. These individualized student objectives will be met in the context of twelve sessions in a self-contained classroom setting.

**2.3 What are the proposed practical arrangements for allocating participants to trial groups?**

The target population for the intervention is made up of secondary school students attending a high

multiethnic density school who have been put in special classes, because of learning or behavioural problems. These classes are comprised of youth who typically have at least a 2 years academic delay. One third of the classes are composed of youth who have not finished their elementary school curriculum. A second third is composed of 7th graders and the third of 8th graders. Some years there may be a few classes of 9th grade. The students are 12 to 17 years of age. The five schools (Saint-Luc, Lucien Pagé, Antoine-de-Saint-Exupéry, La Dauversière and Saint-Henri) taking part in the program and its evaluation were selected on the basis of a long-standing partnership in these projects and because they serve disadvantaged, highly multiethnic communities. These high schools have a large number of special classes: 18 at Lucien Pagé, 16 at St-Luc, 9 at Antoine-de-Saint-Exupéry, 11 at La Dauversière and 9 at Saint-Henri (total: 63) (see table 2). Ten special classes will take part in the theatre program, ten in the group tutoring activity and ten others will constitute a control group. Students who decline to

participate in the research will nevertheless attend the workshops that are part of the class’s regular

curriculum, but they will not participate in the data collection. The ideal evaluative research design would have required that all students who agree to take part in the research project be distributed randomly among the experimental and control groups. Constraints imposed by the functioning of the secondary schools do not allow this, and our evaluative strategy is therefore based on school stratified random assignment to experimental or control status. In an initial stage, a list of the special class homeroom teachers will be drawn up and will form 5 sampling pools, one for each high school. In a second stage, 2 experimental classes, 2 tutoring classes and 2 general curriculum classes will be chosen randomly from each of the 5 sampling pools/schools for a total of 30 classes.

**2.4 What are the proposed methods for protecting against other sources of bias?**

The questionnaires will be filled in by the students themselves in class and by teachers who are not the

homeroom teachers. The teachers who fill in the questionnaires for each student will thus not be present in class with the students for the activity. Even if it cannot be guaranteed that these teachers will be blind to the experimental or control status of the students, given that the students can comment on their activities, they will not be involved in the activities. Lastly, educational achievement is an unbiased source of evaluation, as school marks are given by several different teachers and therefore do not depend solely on the teacher who is in attendance during the activity. At T2, all the teachers involved will be completely blind to the experimental status of the youth. Contamination is another possible bias. The theatre intervention is however quite complex and in our experience has never been implemented spontaneously by teachers who were willing to try it, after discussing with their colleagues. In the case of the tutoring intervention, the added manpower (two resource teachers) is something every teacher in special class would wish to have, but cannot implement independently.

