**Description of the drama workshop program:**

The theatre expression workshops will run for 12 weeks, with one 90-minute workshop per week (only

the contents of the user’s manual, teacher training version, is attached, because of space constraints) (Appendix 1). They will be incorporated into the regular class timetable and will be run by the two members of the intervention team who have training in the theatre and psychology, and the homeroom teacher, whose level of direct involvement will increase gradually as he or she becomes familiar with the workshops. The program is based on playback theatre in the following respects: (1) the purpose of the workshops is to create a safe, respectful environment, in which possible tensions can be explored in the knowledge that they will be contained by the group; (2) artistic performance is not one of the objectives; what is expressed remains within the group and is not presented as a show; (3) the theatrical structure is that of playback theatre: a play director coordinates and contains the story as it unfolds; he or she directs a group of actors (the workshop team and some students) and musicians (students) as they play out a story. Each workshop is structured in more or less the same way. The workshop leaders act as guides and encourage the participants to improvise verbally, musically and through gestures, and to explore alternative scenarios. The workshops are structured on the basis of four types of activities:

1. Warm-up: generally for the first two meetings (sessions 1 and 2), exercises focussing on listening, trust and non-verbal improvisation help participants get to know each other while encouraging play, humour and imagination. The warm-up exercises are done in a respectful, tolerant environment that allows for individual differences while building group solidarity.

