**Secondary outcome:**

1) Emotional and behavioural symptoms will be assessed by the SDQ global scores (teachers and youths

reports). In our study, internal consistency of the self-report version was satisfactory, although not high, for the total SDQ.

2) Impairment (teacher report) will be measured by the SDQ. The internal consistency of the teacher’s version was high (alpha = 0.91 at T1 and 0.90 at T2).

3) Relations with peers will be assessed using the Adolescent Friendship Inventory (AFI) designed by Rubenstein et al. (1989). This 30-item instrument requires the adolescent to indicate to what degree, on a scale of 1 to 5, the feeling expressed by the statement corresponds to his or her personal feelings in relation to his or her network of peers. It is reliable with adolescent refugees (alpha = .88) (105).

4) School performance will be assessed on the basis of the first and the last report cards of the school year (T0 and T1) and with the first report card of the subsequent year (T2). The first report is issued in November, before the beginning of the program, and the last one is issued in June. We will consider students’ grades in mathematics and French, the two compulsory subjects in integration classes. It is to be noted that all the teachers will be blind to the fact that school performance is part of the study assessment and that the mathematics teachers who will not participate in the intervention will also be blind to the experimental versus control status of their students (although schools are small milieu and he may be aware of the fact that some classes are receiving intervention, it is unlikely that he or she will distinguish the type of intervention which is going on).

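### June mathematics and French marks are presented as unbiased and blind-marked, yet the protocol allows them to come from a teacher who took part in or saw the intervention

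*Protocol*

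**What the plan says.** Section 2.4 offers school marks as a safeguard: "educational achievement is an unbiased source of evaluation, as school marks are given by several different teachers". The same sentence concludes only that the marks "do not depend solely on the teacher who is in attendance during the activity".

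Section 2.8/2.9, under secondary outcomes, restricts school performance to mathematics and French. T0 is the November report card, issued before the program starts. T1 is the June card of the same school year, and T2 is the first card of the next year. The section states that "the mathematics teachers who will not participate in the intervention will also be blind to the experimental versus control status of their students", and that no teacher will know that marks are a study outcome. It makes no statement about blinding to arm for whoever marks French.

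Two other sections describe who is in the classroom:

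- Section 2.2.2 (tutoring): "Each self-contained class will include a core teacher who teaches curricula based on the Quebec Education Program with age appropriate competencies in reading, math". It continues: "In each classroom assigned to the tutorship intervention, two academic resource assistants will provide weekly in-class support to students". The individual objectives are "one in math and one in reading per student".
- Section 2.2.1 (theatre): the workshops are run by two team members together with "the homeroom teacher, whose level of direct involvement will increase gradually as he or she becomes familiar with the workshops".

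Secondary hypothesis #6 in Section 1.2 compares theatre or tutoring with control on school performance.

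**The concern.** A mark is a teacher's judgement. It protects against assessment bias only if the marker does not know the arm, or if knowledge of the arm is equal across arms. The protocol claims the first of these for mathematics and implies it for marks in general, but its account of the classes leaves room for the opposite in both active arms.

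If a participating or observing teacher awards the June mark, a change in how that teacher sees the students can appear as a gain in achievement. Control classes have no matching source of change, so the shift would be counted as a program effect under hypothesis #6. Readers would also give the result more weight than it deserves, because the protocol presents marks as its unbiased source.

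**Working it through.** No arithmetic applies beyond counting classes; the check sets the sections side by side.

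1. **Which marks are exposed.** Only the June marks are awarded after the sessions and within the same school year. The November T0 mark precedes the program, so any marking shift in June goes in full into the T0 to T1 change.

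2. **Who teaches the marked subjects.** Section 2.2.2 describes a core teacher in each self-contained class covering reading and mathematics, among other areas. Section 2.4 relies on several markers. Section 2.8/2.9 relies on mathematics teachers who take no part. The protocol does not say how these three descriptions fit together.

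3. **Exposure by arm.** Section 2.3 draws 2 classes per arm from each of 5 schools, so 2 × 5 = 10 classes per arm and 30 in all.

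| Arm | Classes | What a class teacher is exposed to |
|---|---|---|
| Tutoring | 10 | Two assistants in the room each week, working on mathematics and reading objectives |
| Theatre | 10 | Homeroom teacher helps run the sessions, with growing involvement |
| Control | 10 | Neither |

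   The exposure is possible in 10 + 10 = 20 of 30 classes, all on one side of the hypothesis #6 contrast. In a tutoring class, a core teacher who also marks mathematics cannot be unaware of tutoring in that subject. Reading is close to French, though the protocol does not equate the two. In a theatre class, the question is whether the homeroom teacher marks either subject, which the protocol does not say.

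4. **What protection is stated for each mark.** For mathematics there is a claim of non-participation and blindness, softened in the same sentence by the admission that the teacher may know some classes are receiving an intervention. The reassurance offered is that the type of intervention will probably not be recognised. Because hypothesis #6 pools theatre and tutoring against control, knowing that a particular class receives something is enough to unblind that contrast. For French there is no claim of blinding to arm.

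5. **A mechanism in the protocol's own account.** Section 1.3/1.4 reports that the pilot workshops in special classes changed how teachers saw their students. That can move a teacher-awarded mark without a change in achievement.

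6. **The plan's own practice.** Section 2.4 keeps homeroom teachers from completing the teacher questionnaires. No such rule is stated for marks, and the wording on sole dependence concedes that a mark may depend in part on the teacher who attends.

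**The case against.** The strongest reply is that the conflict is inferred. Section 2.2.2 says a class includes a core teacher; it does not say that this is the only teacher, that this person is the homeroom teacher, or that this person awards the report-card marks. Sections 2.4 and 2.8/2.9 point to more than one teacher per class, and the blinding sentence can be read as covering only those mathematics teachers who do not participate. Teachers are also not told that marks are an outcome, which removes much of the motive for favouring a class.

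Much of this stands. A reader might infer that the June marks in the active arms are in fact awarded by participating teachers, so that the safeguard is absent for both subjects. The documents do not support that, because they never identify the marker. They support the narrower statement that such marking is possible and that nothing in the protocol excludes it. Keeping the outcome role of marks from teachers lowers the risk, but it does not blind them to arm or undo a changed view of their students.

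A reader might also infer that the T2 marks should become the main comparison. That would change the question from effect at the end of the program to persistence nine months later. The complete blinding claimed at T2 is asserted in the same section as the claim under question. Expected loss also rises from 5% to about 12% (Section 2.14). The planned time points should stay.

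**Conclusion.** The point holds in limited form. The unbiased label and the blanket claim of blind mathematics teachers are not supported at T1 by the protocol's description of its classes, and French has no assurance of blinding to arm. The June comparison for secondary hypothesis #6 is therefore open to differential marking.

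The scope is one secondary hypothesis, two marks and one time point, with possible exposure in 20 of 30 classes. The self-reported primary outcome is untouched. No size can be put on the bias: the documents give no figure for marking leniency, and the pilot mathematics coefficient in Section 1.3/1.4 is printed without the scale needed to turn it into a yardstick.

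The conclusion assumes only that a core or homeroom teacher may award one of the two marks. If the sponsor can show that in every arm both marks come from teachers who neither attend nor host sessions and do not know the class's arm, the concern falls away.

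**What to change.** 1. Reconcile Sections 2.2.1, 2.2.2, 2.4 and 2.8/2.9 by stating who awards the mathematics and French marks in each arm.
2. Withdraw the description of marks as unbiased and the blanket claim that mathematics teachers are blind at T1. Keep the statement that teachers are not told marks are an outcome, described as a partial safeguard.
3. Record for each mark whether the awarding teacher attended or hosted the sessions.
4. Add a sensitivity analysis of the June marks, restricted to or stratified by non-attending markers where such marks exist, and read it beside the T2 marks already planned.
5. If an arm has few or no such marks, report the June result as unblinded.

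The cost is some rewording, one flag per report-card mark and one extra analysis. If each class has a single marker per subject (an assumption), the flags for June reduce to 30 × 2 = 60 class-by-subject entries. The restricted analysis uses fewer marks and is less precise, and it may not be possible in the tutoring arm if the core teacher marks both subjects. That would itself be worth reporting.

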**2.5 What are the planned inclusion/exclusion criteria?**

All students who are assigned to special classes based on behavioural or learning problems in grades 7-

10 in the participating schools will participate in the program and be included in the study if they and their parents consent to in the research. The natural classroom setting may include non-immigrant youth but they never represent more than 5% of the students in a particular class and they can also benefit from the workshops. The exclusion of more severe cases, although it facilitates the implementation of the intervention (34, 36), does not represent the everyday challenges that teachers encounter in special classes. A real classroom setting provides a better measure of effectiveness (88).

**2.6 What is the proposed duration of treatment period?**

The theatre expression workshops and the tutoring programs will both run for 12 weeks, with one 90-

minute session being held each week.

**2.7 What is the proposed frequency and duration of follow-up?**

Data on the evaluation of the effects of the theatre expression workshops on the students will be

gathered pre- and post-intervention, as well as at follow-up nine months after the end of the intervention. Whenever feasible, the evaluation of the maintenance of the effect of psychosocial interventions for some time (classically 6 months) after termination is a good indicator of their efficacy (34, 36). In the present case, a six month follow up would have resulted in a T2 measure in September, at the beginning of the next school year. This would not have enabled us to assess the medium term effect of the intervention on school performance because the first report card is in November. Furthermore, the teachers’ report Strength and Difficulties Questionnaire (SDQ) is more valid when teachers have been working with the youth for a few months. For these reasons we decided that T2 would be taking place at the beginning of December, 9 months after the end of the intervention. The evaluation questionnaires for each measurement time will be filled in during a 90-minute class period and will be designed so that students with learning difficulties can complete them in approximately 45 minutes. Theoretically all the students taking part will have another school year to finish (high school graduation is at the end of grade 11 in Quebec). However, the youth older than 16 years old who present behavioural and academic difficulties are more at risk to drop out of school than their peers. Nonetheless, in our past studies, the losses attributable to follow-up during a school year have been minimal (< 5%). We therefore do not expect a significant attrition at T2. Special measures will be taken to keep contact with the students who may leave the school at the end of academic school year. Families, who have recently immigrated, are quite mobile. To address potential attrition linked to moving, youth will be asked at T1 if they plan to remain in the same school and/or to move and if so, what is the name of their future school and/or there

new address. Permission to contact them in the future will be requested and contact information for the student will be obtained.

**2.8/2.9 Proposed primary and secondary outcomes measures and their measurement follow up**

The effect of the program on student outcomes, as evaluated by the students and the teachers, will be

measured at the three times by means of a self-report questionnaire. Impairment associated with emotional and behavioural symptoms, intensity of emotional and behavioural symptoms and the social adjustment of the youth will be measured by two informants (youth and teacher) following three main principles: (1) complementarity between the teacher’s perspective and the student’s; (2) maximizing the transcultural validity of the instruments; (3) opting for instruments with robust psychometric properties, given the heterogeneity of the sample.

**Primary outcome: Impairment of emotional and behavioural symptoms reported by youth.** Impairment of emotional and behavioural symptoms will be assessed by the Impact Supplement of the SDQ (101) completed by the adolescents. The SDQ is a 25-item Likert scale assessing emotional and behavioural symptoms. This questionnaire includes an impairment measure that enquires about symptoms in terms of chronicity, distress, social impairment, and burden for others. The SDQ has been translated into more than 20 languages and has been widely used in culturally diverse settings (4, 102,

103). A choice of the French or English version will be offered to the adolescents, and a version in their native tongue will be available on request. The psychometric properties of the SDQ are good (104). In our study, the internal consistency of the self-report Impairment was excellent (alpha = .96).

**Secondary outcome:**

1) Emotional and behavioural symptoms will be assessed by the SDQ global scores (teachers and youths

reports). In our study, internal consistency of the self-report version was satisfactory, although not high, for the total SDQ.

2) Impairment (teacher report) will be measured by the SDQ. The internal consistency of the teacher’s version was high (alpha = 0.91 at T1 and 0.90 at T2).

3) Relations with peers will be assessed using the Adolescent Friendship Inventory (AFI) designed by Rubenstein et al. (1989). This 30-item instrument requires the adolescent to indicate to what degree, on a scale of 1 to 5, the feeling expressed by the statement corresponds to his or her personal feelings in relation to his or her network of peers. It is reliable with adolescent refugees (alpha = .88) (105).

4) School performance will be assessed on the basis of the first and the last report cards of the school year (T0 and T1) and with the first report card of the subsequent year (T2). The first report is issued in November, before the beginning of the program, and the last one is issued in June. We will consider students’ grades in mathematics and French, the two compulsory subjects in integration classes. It is to be noted that all the teachers will be blind to the fact that school performance is part of the study assessment and that the mathematics teachers who will not participate in the intervention will also be blind to the experimental versus control status of their students (although schools are small milieu and he may be aware of the fact that some classes are receiving intervention, it is unlikely that he or she will distinguish the type of intervention which is going on).

